### Recruitment

Sixty participants will be enrolled through hospital bulletin boards, newspapers, and other online advertisements. Those who wish to participate in the study will be enrolled as subjects, after they have gone through the screening process and after obtaining written consent. After the investigator explains the contents of the informed consent form to the participants and ensures that they understand the contents, participants can grant their permission to participate in the study of their own free will. The screening items are as follows: demographic information, medical history, onset time and pattern of insomnia, vital signs, Insomnia Severity Index-Korean (ISI-K), Subjective Cognitive Decline Questionnaire (SCD-Q), Korean Dementia Screening Questionnaire-Cognition (KDSQ-C), and Seoul Neuropsychological Screening Battery (SNSB-D). The SNSB-D includes a Short version of the Geriatric Depression Scale (S-GDS).

### Randomization, allocation concealment, and blinding

Sixty participants who meet the criteria will be assigned to the treatment or control group at a ratio of 1:1 by an investigator independent of this clinical study using the block randomization method. A random assignment table is randomly assigned according to a random number table generated using the RAND function in Excel. According to the randomization table, the investigational drug manufacturer packs the treatment drug and placebo in the same manner, labels the serial number in the form of R-00, and provides it to the principal investigator. Registered pharmacists manage the investigational drugs and provide them to the participants according to their randomization number.

To keep the participants blind, the authenticity of the drug will not be disclosed until the end of the study period. The properties of the placebo are the same as those of the treatment drug, as to maintain double blindness. The investigators, coordinators, and pharmacists should remain blind to the assignments until the end of the study period.

### Intervention

KGT or placebo granules (one dose: 3.0 g) are orally administered with water 3 times a day (30 min after meals) for 12 weeks. KGT is a herbal medicine approved by the Ministry of Food and Drug Safety and is manufactured by Kyoung Bang Pharmaceutical Co., Ltd. (Incheon, Republic of Korea). It is yellow-brown granules and consists of *Astragali Radix* 1.0 g, *Ginseng Radix* 1.0 g, *Atratylodis Rhizoma* 1.0 g, *Poria* 1.0 g, *Zizyphi Fructus* 0.67 g, *Zingiberis Rhizoma* 0.33 g, *Saussureae Radix* 0.33 g, *Glycyrrhizae Radix* 0.33 g, *Zizyphi Spinosi Semen* 1.0 g, *Longan Arillus* 1.0 g, *Angelicae Radix* 0.67 g, *Polygalae Radix* 0.67 g, *Bupleuri Radix* 1.0 g, *Moutan Radicis Cortex* 0.67 g, and *Gardeniae Fructus* 0.67 g. The placebo was manufactured at the National Institute for Korean Medicine Development (NIKOM) Herbal Medicine Production Center (GMP) in Daegu, Republic of Korea, with an appearance, taste, and smell similar to KGT.

The participants will be trained to take the drug three times a day and then return the remaining medication at their next visit. Regarding compliance with the investigational drug, the remaining drug brought in by the participant at the time of the next visit is identified and recorded on a case report form. Medication compliance (%) signifies that the participant’s actual dose is divided by the number of investigational drugs taken by the date of the participant’s visit based on the date of the last visit × 100. The actual dose is the number of returned drugs on the day of the participant’s visit, subtracted from the drugs provided to the participant. When visiting 6 weeks after taking the drugs, the investigator retrieves the unused dose and reversely check the total dose. If medication compliance is less than 60% at the 6th week of taking, the subject will drop out. Even if all doses were administered over the next 6 weeks, the final medication compliance is < 80%. The final medication compliance must be 80% or higher; if medication compliance is less than 80%, the participant is excluded from the per-protocol (PP) analysis group.

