#### Drop-out criteria

The investigators will discontinue the administration of the investigational drug and drop the subjects according to the dropout criteria. The subjects can also voluntarily withdraw from the trial at any time. The criteria for dropout are as follows:When a serious adverse event occurs or when the participant requests discontinuation of the study due to an adverse event.When a systemic disease is found that was not detected in the examination prior to the administration of the investigational drug.In case the participant or the participant’s legal representative requests to discontinue the study.The medication compliance is < 60% at visit 2 (6 weeks after taking the investigational drug).The medication compliance is < 80% at visit 3 (12 weeks after taking the investigational drug).When the participant withdraws consent to participate in the clinical trial.In case the participant is not tracked.In the case of taking drugs that may affect the study results without the investigators’ instruction or consent during the study period.In other cases where the investigators determine that it is inappropriate to proceed with the study.

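### The printed compliance formula divides drug taken by drug taken, and its counting period at visit 3 is unclear; only a cumulative doses-due denominator fits the plan's own 60%-to-80% reasoning

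*Protocol article*

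**What the plan says.** The Intervention section of the protocol article builds compliance in two steps.

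- Numerator: "The actual dose is the number of returned drugs on the day of the participant’s visit, subtracted from the drugs provided to the participant". That is the number of doses taken.
- Denominator: this number is then "divided by the number of investigational drugs taken by the date" on which the participant attends. The reference point for the count is given as "based on the date of the last visit".

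The dosing schedule is "3 times a day (30 min after meals) for 12 weeks".

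Two limits use the result. At week 6: "If medication compliance is less than 60% at the 6th week of taking, the subject will drop out". The reason follows directly: "Even if all doses were administered over the next 6 weeks, the final medication compliance is < 80" (per cent). At the end, compliance must be at least 80% or the participant leaves the per-protocol (PP) set.

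The Drop-out criteria section repeats both limits as grounds for dropping a participant, the second as "The medication compliance is < 80% at visit 3".

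The Statistical analysis section defines PP differently: by completing 12 weeks of product and follow-up to week 24, with no compliance figure. It defines the full analysis set (FAS) as all randomized participants, and the Efficacy analysis section bases the efficacy evaluation on the FAS.

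**The concern.** There are two separate problems in one sentence.

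First, the denominator is worded as drug taken, which is what the numerator already measures. A ratio of a quantity to itself cannot distinguish a compliant participant from a non-compliant one.

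Second, replacing taken by due does not settle the period. The words "based on the date of the last visit" can be read as starting the count at the previous visit. At visit 3 that gives compliance for weeks 6 to 12 only, whereas the justification of the week-6 limit needs compliance over all 12 weeks.

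At stake is who is in the PP set and who meets the visit-3 drop-out criterion. Visit 3 comes before the week-24 PSQI-K, which is part of the primary outcome. The article does not say whether participants dropped at visit 3 are still measured at week 24. If they are not, a misclassification there could also cost a primary measurement in a trial of 60.

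**Working it through.** **Inputs** (all from the Intervention section): 3 doses a day for 12 weeks; limits of 60% at week 6 and 80% at the end; doses taken = supplied minus returned. I assume visits fall exactly at 42 and 84 days.

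- Doses due by week 6: 3 × 42 = 126
- Doses due by week 12: 3 × 84 = 252
- 60% of 126 = 75.6, so 75 doses fail and 76 pass
- 80% of 252 = 201.6, so 201 doses fail and 202 pass

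**The plan's own statement, cumulative reading.** Compliance = doses taken since baseline / doses due since baseline × 100.

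- 75 doses by week 6: 75/126 = 59.5%. With every later dose taken: (75 + 126)/252 = 201/252 = 79.8%, below 80%.
- 76 doses by week 6: 76/126 = 60.3%. With every later dose taken: (76 + 126)/252 = 202/252 = 80.2%, which reaches 80%.
- In general, (60% + 100%)/2 = 80%.

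The stated link between the two limits is reproduced exactly.

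**Literal reading.** Compliance = taken / taken × 100 = 100% for any number of doses from 1 upward. Neither limit is ever reached.

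**Interval reading.** Compliance = doses taken since the previous visit / doses due since the previous visit × 100.

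- Week 6: the interval starts at baseline, so the result equals the cumulative one.
- Week 12: the denominator is 126. After 75 doses by week 6 and full dosing thereafter, the result is 126/126 = 100%. The plan says it must be below 80%, so this reading contradicts the plan's reasoning.

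**Where the two doses-due readings part at visit 3:**

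| Doses weeks 0–6 | Doses weeks 6–12 | Interval | Cumulative |
|---|---|---|---|
| 76 | 101 | 101/126 = 80.2%, passes | 177/252 = 70.2%, fails |
| 126 | 88 | 88/126 = 69.8%, fails | 214/252 = 84.9%, passes |

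Both participants pass the week-6 limit, so both would reach visit 3. Across all pairs of counts with 76 to 126 doses in the first interval and 0 to 126 in the second (51 × 127 = 6,477 pairs), 325 pass by interval and fail cumulatively, and 325 do the reverse. These are counts of possible combinations, not probabilities; they show only that disagreement runs in both directions.

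**The case against.** The strongest reply is that this is a wording slip with a recoverable meaning. A measure that is always 100% would make both limits pointless, so taken must stand for to be taken. The Intervention section speaks of final compliance, has the investigator work back to the total dose at week 6, and gives a justification that is true only cumulatively. A careful reader can reach the right formula from the same paragraph. The previous-visit reading is one reading of an unclear phrase, makes no difference at week 6, and is contradicted by its context at week 12. The one arithmetic statement that the plan makes is correct. The article also condenses a fuller protocol in which the instructions for counting may be clearer.

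Most of this stands, and it limits the point. A reader might infer that the 60% and 80% rules cannot be operated at all, or that in practice nobody would ever fail them. The document does not support that, because its own reasoning shows what was meant. A reader might also infer that the main efficacy result depends on the formula. It does not do so through set membership: the FAS is all randomized participants, and PP is supportive.

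What the reply does not remove is that the printed formula gives a wrong result if followed. Condensation explains missing detail, not a formula, a limit and a rationale that are all printed and disagree. That the definition has to be inferred from its justification is the reason to correct it.

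**Conclusion.** The point holds in a limited form. As printed, the denominator is wrong. Once it is read as doses due, the counting period at visit 3 is ambiguous, and one available reading conflicts with the paragraph's own reasoning. The cumulative reading is the one that fits.

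The size for an individual can be large: the examples differ by 10 percentage points (80.2% against 70.2%) and 15.1 percentage points (84.9% against 69.8%), and fall on opposite sides of the 80% limit. How many of the 60 participants would be classified differently cannot be derived from the document.

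The consequence is confined to the supportive PP set and the visit-3 drop-out criterion. FAS membership is unaffected. Any loss of week-24 data is conditional on dropped participants not being followed, which the article leaves open.

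The dose counts assume visits on schedule. Other visit dates change 126 and 252, but not the conflict between the readings.

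**What to change.** For the analysis variable that defines the PP set, replace the formula by:

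compliance (%) = (doses dispensed minus doses returned, summed from baseline to the visit) / (doses scheduled from baseline to the visit) × 100.

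State that returns at week 6 are included in the week-12 total. This matches the plan's own 60%-to-80% arithmetic.

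Reconcile the two PP definitions: the Intervention section excludes participants below 80%, while the Statistical analysis section names completion only. The formula alone does not resolve that.

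Reconcile the wording of the Drop-out criteria with the Intervention section, so that it is clear which compliance figure each refers to. No threshold needs to change for this point, and none is proposed; nor is any rule for stopping treatment.

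The cost is one sentence in the protocol and in the case report form instructions, plus the alignment of the two PP definitions. Remaining drug is already recorded on the case report form, so compliance can be recomputed for participants already enrolled, provided the amounts dispensed were recorded too.

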### Outcome measurements

The PSQI-K and ISI-K are evaluated to confirm the effect of KGT granules on insomnia in the elderly. This will be measured three times: before taking the investigational drug, at the end of 12 weeks of medication, and after 12 weeks of 12-week medication.

To evaluate cognitive function, the SNSB-D is measured twice: at screening and at the end of 12 weeks of medication. In addition, to evaluate quality of life, SF-36 is measured three times: before taking the investigational drug, at the end of 12 weeks of medication, and after 12 weeks of the 12-week medication. The S-GDS, which evaluates depression, is measured twice in total: before taking the investigational drug and at the end of 12 weeks of medication.

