### Safety assessments and monitoring

Adverse events will be investigated during each visit. Subjects who took the investigational drug at least once are eligible for safety analysis. Any undesirable medical findings indicating symptoms not observed prior to the study are considered adverse events.

At every visit, blood pressure, pulse rate, and body temperature are investigated to determine the participants’ health status. Laboratory tests for glucose, aspartate aminotransferase (AST), alanine aminotransferase (ALT), blood urea nitrogen (BUN), creatinine, sodium, potassium, chloride, lactate dehydrogenase (LDH), creatine phosphokinase (CPK), and electrocardiography (ECG) are investigated before taking the investigational drug and after 6 and 12 weeks of medication. Participants with abnormal laboratory test results should be followed up. Additionally, total cholesterol, HDL cholesterol, LDL cholesterol, triglyceride, homocysteine, T3, free T4, and thyroid stimulating hormone (TSH) levels are investigated at baseline.

After visit 1 (baseline), the investigators monitor status of medication, adverse events, and concomitant medications via phone calls once a week until the next visit. After the end of the medication at visit 3 (12 weeks), the investigators monitor adverse events and concomitant medications via phone call every two weeks until the final visit.

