#### Efficacy analysis

Efficacy evaluation is based on the FAS analysis group, and efficacy is analyzed and presented with reference to the PP analysis group. For safety evaluation, the ITT analysis group is the main assay.

Analysis of primary efficacy endpoints.

Participants with PSQI-K scores before the study and at least once after consuming the investigational product are analyzed. Based on the baseline, the difference between the two groups in the total PSQI-K score change at weeks 12 and 24 is analyzed using repeated measures analysis of variance (RM ANOVA) and linear mixed model (LMM) methods.

2)Analysis of secondary endpoints.

The PSQI-K score change will be analyzed by a paired t-test within each group for changes at 12 and 24 weeks based on the baseline. The ISI-K score change will be analyzed using the paired t-test within each group and the independent t-test between the two groups at the 12-week dosing period and at 24 weeks based on the baseline. The SNSB-D and S-GDS score changes will be analyzed using the paired t-test within each group and the independent t-test between the two groups with respect to the score change at week 12, based on the baseline. The SF-36 score change will be analyzed using a paired t-test within each group and an independent t-test between the two groups at 12 and 24 weeks based on the baseline. Changes over time will be analyzed using the RM ANOVA and LMM methods. The estimated values of the mean difference between the groups, 95% confidence intervals, and p-values will be presented.

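### The PSQI-K is not taken at the existing week-6 visit, so a participant dropped between weeks 6 and 12 appears to leave no post-baseline primary score

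*Protocol article*

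**What the plan says.** All references are to the Protocol article.

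- **Assessment times.** Outcome measurements, on the PSQI-K and ISI-K: "This will be measured three times: before taking the investigational drug, at the end of 12 weeks of medication", with the third measurement 12 weeks after medication ends. Study design and Primary outcome give the same times.
- **Week-6 visit.** Visit 2 is at week 6. Unused drug is counted there (Intervention). Laboratory tests and ECG "are investigated before taking the investigational drug and after 6 and 12 weeks of medication" (Safety assessments and monitoring). No efficacy questionnaire is placed there in the text.
- **Removal at week 6.** One drop-out criterion reads "The medication compliance is < 60% at visit 2 (6 weeks after taking the investigational drug". Intervention repeats it: "If medication compliance is less than 60% at the 6th week of taking, the subject will drop out". Under Drop-out criteria the investigators will "discontinue the administration of the investigational drug and drop the subjects according to the dropout criteria". Other criteria, such as a serious adverse event, withdrawn consent or unapproved drugs, can also apply before week 12.
- **Who is analysed.** Efficacy analysis: "Participants with PSQI-K scores before the study and at least once after consuming the investigational product are analyzed". The endpoint is stated as "the difference between the two groups in the total PSQI-K score change at weeks 12 and 24 is analyzed", using RM ANOVA and LMM. Statistical analysis defines the full analysis set as everyone randomised.

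**The concern.** An LMM reduces attrition bias only through scores seen before a participant leaves. Here the first score on treatment is at week 12. A participant who attends visit 2 and leaves before week 12 has been seen on treatment but contributes nothing on early response. If the LMM is fitted to change from baseline, that person has no record at all. If baseline is modelled as an outcome, that person adds a baseline value only.

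What is at stake is the between-group difference at week 12. If leaving depends on how sleep responded in the first six weeks, and does so differently in the two arms, those who remain are a selected group and the model cannot correct for it. A week-6 score that was never collected cannot be supplied later by an analysis plan.

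**Working it through.** **1. Trace one participant dropped at week 6.** PSQI-K before drug: 1. PSQI-K at week 6: 0, none scheduled. PSQI-K at weeks 12 and 24: 0, if being dropped ends assessment; the text describes none afterwards. Post-baseline total: 0. The primary-analysis rule needs at least 1, so the participant is excluded.

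**2. Inputs for the size.** From the documents: 30 per group, 1:1 allocation. There is no effect size, SD, power or drop-out rate to reproduce, because Sample size rests the 30 per group on the central limit theorem. Everything else below is an assumption.

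**3. Large-sample check, one arm, no baseline adjustment.** Let ρ be the correlation between week-6 and week-12 change, and m the amount, in SD units, by which mean week-6 change differs between those retained and the whole arm. Then

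bias in that arm's week-12 mean change = ρ × m (SD units).

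Drop-out was logistic in week-6 response, with slope 1.5 per SD.

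| Lost in the arm | m | ρ = 0.5 | ρ = 0.7 | With week-6 score |
|---|---|---|---|---|
| 10% | 0.12 | 0.06 SD | 0.09 SD | about 0 |
| 20% | 0.22 | 0.11 SD | 0.16 SD | at most 0.004 SD |

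The bias in the treatment difference is one arm's bias minus the other's. It cancels if the mechanism is the same in both arms, equals the tabled value if only one arm is affected, and doubles if the arms go in opposite directions.

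In points: with score SD 3.5 and baseline correlation 0.5, the SD of change is 3.5 × √(2 × (1 − 0.5)) = 3.5. The one-arm bias is then 0.061 × 3.5 = 0.21 to 0.085 × 3.5 = 0.30 points at 10% lost, and 0.110 × 3.5 = 0.39 to 0.157 × 3.5 = 0.55 points at 20% lost.

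**4. Simulation at the trial's size.** 30 per arm, SD 3.5, correlations 0.5 to 0.7, about 15% lost depending on week-6 response, week-12 difference.

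| Loss mechanism | Absolute bias without week 6 (points) |
|---|---|
| Same in both arms | 0.01 (true difference 0); 0.04 (true difference −2) |
| One arm only | 0.23 |
| Opposite directions by arm | 0.25 to 0.51 |

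The top of the last row comes from a true difference of −2 estimated as −1.49: −1.49 − (−2) = 0.51. The same runs with a week-6 score gave −2.01, a bias of −0.01. With a true difference of 0, the estimates were 0.41 without the score and −0.02 with it.

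The one-arm figure is lower than most of step 3 because baseline adjustment removes part of the bias and the loss is 15% rather than 20%.

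**5. Scale.** The standard error is about 0.84 to 0.87 points in every case and is essentially unchanged by a week-6 score. The worst case in step 4 is 0.51 / 0.85 = 0.6 of a standard error. The gain is in bias, not precision.

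**The case against.** The schedule contradicts nothing. The PSQI-K times match the primary times exactly, and week 6 is a compliance and safety visit. A reader might infer that the assessment plan is in error; it is not. This is a design choice that could cheaply be improved.

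The missing week-6 score is also not the main cause of the loss. Dropped participants lack a week-12 score because they are dropped, and they leave the analysis because the rule requires a post-dose score, which sits badly with a full analysis set of everyone randomised. A week-6 value is not a week-12 or week-24 outcome. This stands, and the fix has to reflect it.

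A reader might infer that everyone dropped at week 6 certainly lacks a later score. The documents do not go that far: Table 1 is not shown, the article condenses a fuller protocol, and an early-termination assessment may exist there.

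A reader might also infer a bias of about half a point. That needs response-driven loss in opposite directions by arm. In a double-blind trial with a matched placebo, a similar mechanism in both arms is at least as plausible, and the bias is then near zero. The week-6 rule is triggered by compliance, not by PSQI-K response, and nothing in the documents shows that the week-6 score would explain who leaves. The loss is therefore not shown to be beyond recovery without the score, nor sure to be missing at random with it.

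Finally, the score would not help a complete-case RM ANOVA, participants lost before week 6, or loss that it does not explain.

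**Conclusion.** The point holds as a low-cost improvement, not as an error in the plan. On the text shown, a participant dropped at or after week 6 but before week 12 has no post-baseline PSQI-K, is excluded from the primary analysis, and leaves the LMM nothing to work with, although a visit on treatment took place.

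The size is unknown. Under the assumptions of 30 per arm, SD 3.5 and about 15% response-dependent loss, the bias in the week-12 difference runs from about 0, through about 0.2, to 0.25 to 0.5 points, according to whether the mechanism is shared, confined to one arm or opposite by arm. Heavier loss without baseline adjustment would give more (step 3). A week-6 score brings the bias to about 0 only in the LMM and only if the loss is missing at random given that score. Ending follow-up at drop-out remains the main cause, and a week-6 score only partly offsets it.

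**What to change.** 1. Give the PSQI-K, and the ISI-K, at visit 2 before the compliance decision is made.
2. Include week 6 as a visit in the LMM, with weeks 12 and 24 kept as the primary times. State that a participant with a week-6 score only enters the LMM without a value at either primary time. Participants already past week 6 have that value missing.
3. Continue PSQI-K collection at weeks 12 and 24 for participants who stop the drug, where they agree. This addresses the main cause directly. Telephone contact is already planned weekly after baseline and every two weeks after visit 3, so continued contact looks feasible. It concerns data collection only and leaves the rules for stopping the drug as they are.

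The cost is a few minutes of participant time at a visit already held, the further assessments under item 3, and an ethics amendment. Trial status reports 8 of the planned 60 enrolled on 25 August 2023, so at that date 60 − 8 = 52 were still to come. Sample size and primary endpoint do not change.
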